# Assessing the Effectiveness and Acceptability of a Personalized Mobile Phone App in Improving Adherence to Oral Hygiene Advice in Orthodontic Patients: Protocol for a Feasibility Study and a Randomized Controlled Trial

**DOI:** 10.2196/18021

**Published:** 2021-01-13

**Keywords:** orthodontics, adherence, smartphone apps, mobile phone apps, personalized health care, information provision

## Abstract

**Background:**

Orthodontic treatment is a common health care intervention; treatment duration can be lengthy (2-3 years on average), and adherence to treatment advice is therefore essential for successful outcomes. It has been reported that up to 43% of patients fail to complete treatment, and there are currently no useful predictors of noncompletion. Given that the National Health Service England annual expenditure on primary-care orthodontic treatment is in excess of £200 million (US $267 million), noncompletion of treatment represents a significant inefficient use of public resources.
Improving adherence to treatment is therefore essential. This necessitates behavior change, and interventions that improve adherence and are designed to elicit behavioral change must address an individual’s capability, opportunity, and motivation. Mobile phones are potentially an invaluable tool in this regard, as they are readily available and can be used in a number of ways to address an individual’s capability, opportunity, and motivation.

**Objective:**

This study will assess the effectiveness and acceptability of a personalized mobile phone app in improving adherence to orthodontic treatment advice by way of a randomized controlled trial.

**Methods:**

This study will be conducted in 2 phases at the Eastman Dental Hospital, University College London Hospitals Foundation Trust. 
Phase 1 is feasibility testing of the My Braces app. Participants will be asked to complete the user version of the Mobile Application Rating Scale. The app will be amended following analysis of the responses, if appropriate. 
Phase 2 is a randomized controlled trial to test the effectiveness and acceptability of the My Braces app.

**Results:**

This study was approved by the London – Bloomsbury Research Ethics Committee on November 5, 2019 (reference 19/LO/1555). No patients have been recruited to date. The anticipated start date for recruitment to phase 1 is October 2020.

**Conclusions:**

Given the availability, affordability, and versatility of mobile phones, it is proposed that they will aid in improving adherence to treatment advice and hence improve treatment completion rates. If effective, the applicability of this methodology to developing behavior change/modification interventions and improving adherence to treatment across health care provides an exciting opportunity.

**Trial Registration:**

ClinicalTrials.gov NCT04184739; https://clinicaltrials.gov/ct2/show/NCT04184739

**International Registered Report Identifier (IRRID):**

PRR1-10.2196/18021

## Introduction

### Overview

Orthodontic treatment is a common health care intervention; the most recent National Child Dental Health Survey (England, Wales, and Northern Ireland) indicated that 9% of 12-year-old children are receiving orthodontic treatment, and a further 37% have an unmet need [1]. Treatment duration can be lengthy (2-3 years on average), and adherence to treatment advice is therefore essential for successful outcomes [2]. Failure to adhere to treatment advice can mean that treatment objectives are not met, and there may be detrimental effects on dental health. For example, failing to adhere to dietary advice may result in breakage of the braces and increased overall treatment time, and nonadherence to dietary and oral hygiene advice during treatment can lead to avoidable tooth decay and gum disease.

The National Health Service (NHS) experiences significant costs as a result of nonadherence to treatment [3], and orthodontics is no exception to this. One multicenter study found that 43% of patients failed to complete treatment, and there were no useful predictors for this [4]. To put this into perspective, the NHS England annual expenditure on primary-care orthodontic treatment alone is in excess of £200 million (US $267 million) [5]; noncompletion of treatment therefore represents a significant inefficient use of public resources.

Improving adherence is complex and necessitates a change or modification of existing behavior. A contemporary and widely accepted framework based on multiple models of behavior change developed by Michie et al [6] is the behavior change wheel (BCW). The COM-B model forms the core of the BCW and proposes that individuals need capability (C), opportunity (O), and motivation (M) to perform or adapt a particular behavior (B).

Attempts to improve adherence to treatment advice in orthodontics have included utilizing mind maps and multimedia-assisted methods of providing information. Although these methods have been shown to significantly increase knowledge [7-9], this does not necessarily equate to better adherence to treatment advice or better outcomes [8]. A recent systematic review considered techniques including the use of motivational tests, the Hawthorne effect, and the use of awards and rewards, concluding that there is insufficient evidence to recommend a single method to improve patient adherence to treatment and that more research is required in this area [10].

Mobile phones are potentially an invaluable tool in improving adherence; they are capable of delivering both generic and personalized treatment information (for example, appointment and toothbrushing reminders) in a variety of formats (eg, visual, text, video). Ultimately, several methods for improving adherence can be delivered with a single resource. In orthodontics, mobile phones could serve to improve adherence to treatment advice, in particular adherence to oral hygiene advice, as this has been shown to be problematic in orthodontic patients. Previous research has highlighted that plaque levels in patients with fixed orthodontic appliances are 2 to 3 times higher than plaque levels in nonorthodontic patients [11]; it is crucial to optimize oral hygiene as poor oral hygiene can result in gingivitis and demineralization.

In 2019, a paper summarizing the availability of orthodontic-related apps found that 305 apps were available on the Apple App Store and Google Play Store in the United Kingdom [12]. However, to date there are very few studies assessing the effectiveness of apps for orthodontic patients. A recent systematic review that aimed to assess the effectiveness of interventions delivered by mobile phones (including apps) in improving adherence to oral hygiene advice for children and adolescents concluded that mobile phones were found to be effective [13]. However, the generalizability of these results is limited due to the small number of trials included (n=2) and the unclear risk of bias of the included studies [13]. Additionally, none of the included studies assessed the effectiveness of personalized information provision, despite evidence that personalized communication in health care is more effective than nonpersonalized communication in relation to changing health-related behaviors [14]. More recently, a pilot study demonstrated the potential effectiveness of a chat room via a mobile phone app in improving appointment attendance and reducing relapse in patients wearing retaining braces [15]. Furthermore, a randomized controlled trial assessing the effectiveness of a personalized mobile phone app in supporting orthodontic patients during fixed appliance treatment demonstrated the potential for improvement in oral hygiene at 3 months into treatment, with the app group demonstrating a greater reduction in gingival bleeding and plaque scores [16].

To date, there have been no randomized controlled trials published in orthodontics assessing the effectiveness of behavior change interventions designed using the BCW. In light of this, an app called “My Braces”, which is grounded in behavior change theory, has been developed by the research team in order to provide generic and personalized orthodontic treatment information. The personalized element allows patients to input their own treatment information (including progress photographs), set goals, and develop plans for achieving these goals and provides the patient and clinicians with appropriate dashboards to monitor progress. Ultimately, this app aims to improve adherence to orthodontic treatment advice. For the purposes of this study, the My Braces app has been designed to allow three different levels of access and functionality:

Version 1 includes a toothbrushing timer only.

Version 2 includes a toothbrushing timer and generic treatment information (a combination of images and text).

Version 3 includes a toothbrushing timer; generic treatment information; access to input patient-specific personalized treatment information (including progress photographs), set goals, and develop plans for achieving these goals; and appropriate dashboards for the patient and clinicians to monitor progress.

The longitudinal nature of orthodontic treatment makes this an ideal opportunity to assess the effectiveness of new ways to provide information in order to improve adherence to treatment advice. If found effective, the applicability of this methodology to improve adherence across health care provides an exciting opportunity.

### Aims

This study will assess the quality, effectiveness, and acceptability of the My Braces app and test the following primary hypothesis:

Using the full functionality of the My Braces app improves adherence to oral hygiene advice in patients undertaking fixed brace treatment.

The secondary hypothesis is as follows:

Using the full functionality of the My Braces app improves adherence to orthodontic treatment advice (reduction in fixed appliance breakages, missed and rescheduled appointments, treatment duration, number of appointments, and enamel demineralization).

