#### Data Collection

A complete data set will be collected at baseline, 3 months into treatment, 12 months into treatment, and at the end of treatment when the orthodontic appliances have been removed.

Two primary outcome measures have been selected, a health behavior outcome and a clinical outcome, as both are felt to be important. The outcome measures are timed toothbrush use and gingival bleeding scores (these scores indicate the amount of bleeding from the gums, where bleeding is an indicator of inadequate toothbrushing).

The secondary outcomes of interest are as follows: plaque scores, which indicate the amount of plaque on the teeth, where retention of plaque is an indicator of inadequate toothbrushing; number of fixed appliance breakages; number of missed and rescheduled appointments; treatment duration, number of appointments (including emergency appointments for appliance breakages); enamel demineralization (early tooth decay) on the upper anterior six teeth (using standardized photographs), as demineralization is a further indicator of inadequate toothbrushing and nonadherence to the appropriate diet; subjective quality of the app (sections E and F of the uMARS questionnaire); and app engagement.

The following baseline measurements and details will be obtained prior to treatment commencing: age, gender, malocclusion (type of dental bite), whether or not extractions (removal of teeth) are required for treatment, clinical photographs of the teeth (these will be compared with completion of treatment photographs to assess for enamel demineralization), bleeding score, and plaque score.

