#### Planned Analyses

Proposed outcome analyses are summarized in Table 2.

For each of the main outcome measures, it is anticipated that regression analysis will be undertaken. The main factor of interest (group allocation) and confounding variables (eg, age, gender, ethnicity) will be entered into univariable regression analyses to determine the level of significance and to limit the number of variables entered into the multivariable analysis. Any factors with *P*≤.10 will be considered for inclusion in the multivariable analysis. Factors with *P*<.05 in the multivariable analysis will be considered as having a significant effect on toothbrushing time or gingival bleeding. Secondary outcomes will be explored in a similar manner.

If necessary, an intention to treat analysis will be performed; all enrolled and randomized patients will be included in the analysis and analyzed in the groups to which they were randomized.

**Table 2 table2:** A summary of proposed statistics for outcome analysis.

Outcomes	Method of analysis
Toothbrushing duration	Comparison of the 3 groups using an ANOVA, followed by 2-sample *t* tests (A vs B, B vs C, and A vs C) if any statistical significance is found
Bleeding score	Chi-square test
Plaque scores	Comparison of the 3 groups using an ANOVA, followed by 2-sample *t* tests (A vs B, B vs C, and A vs C) if any statistical significance is found
Number of breakages	Kruskal-Wallis test, followed by Mann-Whitney test (A vs B, B vs C, and A vs C) if any statistical significance is found
Number of missed appointments	Kruskal-Wallis test, followed by Mann-Whitney test (A vs B, B vs C, and A vs C) if any statistical significance is found
Total number of appointments	Kruskal-Wallis test, followed by Mann-Whitney test (A vs B, B vs C, and A vs C) if any statistical significance is found
Treatment duration	Comparison of the 3 groups using an ANOVA, followed by 2-sample *t* tests (A vs B, B vs C, and A vs C) if any statistical significance is found
Enamel demineralization	Chi-square test
App subjective quality	Comparison of the 3 groups and different section of the uMARS form by using the Kruskal-Wallis test.
App engagement	Comparison of the 3 groups using an ANOVA, followed by 2-sample *t* tests (A vs B, B vs C, and A vs C) if any statistical significance is found

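### Treatment duration, appointments and breakages are compared as totals without regard to completion or time in treatment, so these secondary comparisons are biased if abandonment differs by arm

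*Protocol article*

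**What the plan says.** The Aims section states the secondary hypothesis as improved adherence, spelled out as a "reduction in fixed appliance breakages, missed and rescheduled appointments, treatment duration, number of appointments, and enamel demineralization". Lower is better for each item, and nothing makes this conditional on treatment having been completed.

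The phase 2 Data Collection section lists the outcomes as plain quantities, for example "treatment duration, number of appointments (including emergency appointments for appliance breakages", and places the final assessment at removal of the appliances. It does not separate planned completion from early removal. Under Other Outcomes, duration and the counts of breakages and appointments come from the medical records.

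Table 2 (Planned Analyses) gives for treatment duration: "Comparison of the 3 groups using an ANOVA, followed by 2-sample *t* tests (A vs B, B vs C, and A vs C"). For breakages, missed appointments and total appointments it gives: "Kruskal-Wallis test, followed by Mann-Whitney test (A vs B, B vs C, and A vs C) if any statistical significance is found". The text above the table adds that secondary outcomes will also be explored by regression, with age, gender and ethnicity as example covariates. An intention-to-treat analysis of all randomized patients is to be done if necessary.

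The Introduction motivates the trial by non-completion: "One multicenter study found that 43% of patients failed to complete treatment". The Abstract's Conclusions expect the app to help in "improving adherence to treatment advice and hence improve treatment completion rates", and the Discussion says much the same. Completion is neither in the list of outcomes nor in Table 2.

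**The concern.** Duration, number of appointments and number of breakages all accumulate with time in treatment. A patient who abandons treatment has less of each, and the secondary hypothesis reads less as better. An app that keeps patients in treatment could therefore appear to lengthen treatment and to increase visits and breakages. An app that drives patients away could appear to help.

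Leaving early stoppers out does not solve this. Those who complete are selected by an event after randomization that is itself a form of adherence, so the randomized comparison is lost.

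The secondary hypothesis is the protocol's only test of adherence beyond oral hygiene. Three of its listed measures are open to this problem.

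**Working it through.** The plan states no expected duration, count or completion rate for its own patients, so there is no figure of its own to reproduce. The inputs are:

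- From the document: 43% non-completion (Introduction, from a cited study), so 57% completion; average treatment of 2 to 3 years, of which 30 months is the midpoint; 46 patients per group (Sample Size).
- Assumed: 70% completion in the better-retained arm; leavers stop at 14 months (range 8 to 20); the app changes nothing else.

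**Early stoppers included as recorded.** Mean duration = (completion share × 30) + (non-completion share × leaving time).

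| Leavers stop at | 57% complete | 70% complete | Difference | Ratio |
|---|---|---|---|---|
| 8 months | 17.10 + 3.44 = 20.54 | 21.00 + 2.40 = 23.40 | 2.86 | 1.14 |
| 14 months | 17.10 + 6.02 = 23.12 | 21.00 + 4.20 = 25.20 | 2.08 | 1.09 |
| 20 months | 17.10 + 8.60 = 25.70 | 21.00 + 6.00 = 27.00 | 1.30 | 1.05 |

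The difference is 0.13 × (30 − leaving time). If visits and breakages occur at a constant monthly rate that is equal in both arms, expected totals follow the ratio column and are 5% to 14% higher in the better-retained arm. At 14 months, a true fall in the breakage rate of 1 − 23.12/25.20 = 8% would be fully hidden.

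**Other scenarios.** With abandonment pA and pC in groups A and C, and leavers stopping at fraction f of a course of T months, the difference in mean duration is (pA − pC)(1 − f)T. The ratio of totals is [1 − pC(1 − f)]/[1 − pA(1 − f)]. With f = 0.5 and T = 24 to 36:

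- 43% to 21.5%: 0.215 × 0.5 × T = 2.6 to 3.9 months; ratio 0.8925/0.785 = 1.14.
- 20% to 10%: 0.10 × 0.5 × T = 1.2 to 1.8 months; ratio 0.95/0.90 = 1.06.
- Equal abandonment: difference 0, ratio 1. If 57% complete in both arms and leavers are unaffected, a true difference of d months among completers appears as 0.57d. That is dilution, not reversal.

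**Size against chance.** Assume a within-status SD of 6 months and the 16-month gap between completers and leavers. The variances are 36 + 0.57 × 0.43 × 256 = 98.7 and 36 + 0.70 × 0.30 × 256 = 89.8. The standard error of the difference is √[(98.7 + 89.8)/46] = 2.0 months, so the 2.1-month artefact is about one standard error.

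A simulation with the stronger contrast (43% versus 21.5%) and no true effect used 46 per group, completed courses of about 30 months (SD 6), leavers stopping at 10% to 90% of their course, 0.67 visits and 0.1 breakages per month. Pairwise P<.05 in the wrong direction occurred in about 36% of trials for duration, 25% for appointments and 13% for breakages, against about 2% with equal abandonment. These tests were run without the preceding three-group test that Table 2 requires. In the same simulation the ratio of breakages per month of treatment was about 1.01, so the artefact is absent from the rate.

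**Early stoppers excluded.** No arithmetic is needed. With 57% and 70% completing, the two sets of completers are differently selected parts of their arms.

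**The case against.** The strongest objection is that the article prescribes no scoring rule for early stoppers. A reader might infer that the plan counts abandonment as success. The text does not say so: intention to treat applies only if necessary, 20% dropout is allowed for, and details of censoring may sit in an analysis plan that is not shown. This stands, and the point is therefore conditional. The use of medical records and the intention-to-treat sentence suggest inclusion but do not settle it. What the article does fix is the direction of benefit and the tests on totals, and neither way of handling early stoppers makes those tests sound.

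It can also be said that the regression has an open covariate list, so time in treatment is not ruled out. That is true, but it is not named, and Table 2 does not use it.

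Third, a reversed sign needs abandonment to differ by arm, the 43% comes from another study, and the central illustration is only about one standard error. All of this stands. Differential completion is, however, what the protocol proposes the app will bring about.

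A reader might go further and infer that all the secondary conclusions, or the trial's main aim, are reversed. The documents do not support that. Missed appointments may rise among patients who are drifting away. Plaque score is a percentage of surfaces and does not accumulate. The primary hypothesis concerns oral hygiene, and completion appears only as background and hope.

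**Conclusion.** The point holds in conditional form. The protocol defines less treatment time, fewer visits and fewer breakages as better adherence and tests totals that ignore completion and time in treatment. If abandonment differs by arm, these comparisons are biased and can have the wrong sign; if it does not, they are diluted. With early stoppers included as recorded, the illustration gives 2.1 months of spurious extra duration (2.9 to 1.3) and totals 5% to 14% higher. This rests on the assumed 70% completion, course lengths and constant rates; only the 43% and the 2-to-3-year average come from the document. Primary outcomes and sample size are unaffected. The change should be made, because the protocol's own rationale predicts the condition under which these analyses mislead.

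**What to change.** - State how patients who stop early enter each analysis.
- Add treatment completion (yes/no) as a secondary outcome, with a definition set by the investigators and a recorded stop date and status.
- Analyse duration as time to completed treatment with early stopping as a competing event, and show cumulative incidence by arm.
- Analyse breakages and missed or rescheduled appointments as rates, by negative binomial regression with log time in treatment as offset.
- Report total appointments alongside completion status, not as a stand-alone adherence measure. Dividing them by time would remove part of the hypothesized benefit if the app truly shortens treatment.

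Raw counts over the first 12 months are not a substitute unless they too are adjusted for time in treatment, because a patient who leaves at month 8 still has fewer months in which to accumulate them.

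The cost is slightly more analysis work and one extra item, completion status, to extract from the medical records. That item is not among those the article lists. The Consent Process section records a reason only for withdrawal from the study, and only if the participant gives one. No extra visits or patients are needed.

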## Methods

This study will be conducted in 2 phases at the Eastman Dental Hospital (EDH), University College London Hospitals (UCLH) Foundation Trust, London, United Kingdom.

### Consent Process

A member of the direct care team (the clinician undertaking treatment) will ask eligible patients if they would be prepared to consider involvement in the study. Children younger than 16 years will only be approached if accompanied by a parent/legal guardian. All prospective participants will be provided with patient information leaflets and will be given ample opportunity to ask questions about the study before enrolling. Participants will be required to provide written informed consent to participate in the study. For participants younger than 16 years, parents/legal guardians will also be required to provide written informed consent for their child to participate in this study. Contact details for a designated member of the research team will be provided, and patients will be informed that they may withdraw from the study at any point if they wish to do so. If this happens and participants give a reason for doing so, that reason will be recorded. Withdrawing from the trial will not affect treatment in any way. Signed consent and assent for inclusion will be obtained by a member of the research team. All members of the team have undertaken training in research ethics, including completion of Good Clinical Practice in Secondary Care. Example consent forms can be obtained by contacting the corresponding author.

### Phase 1

Phase 1 is a feasibility study with a convenience sample of patients at different stages of treatment. The purpose of this phase is to assess whether the app is deemed to be of high quality by end users.

